## Abstract

**Background:**

To work towards reaching the WHO goal of eliminating soil-transmitted helminth (STH) infections as a public health problem, the total number of children receiving anthelmintic drugs has strongly increased over the past few years. However, as drug pressure levels rise, the development of anthelmintic drug resistance (AR) is more and more likely to appear. Currently, any global surveillance system to monitor drug efficacy and the emergence of possible AR is lacking. Consequently, it remains unclear to what extent the efficacy of drugs may have dropped and whether AR is already present. The overall aim of this study is to recommend the best diagnostic methods to monitor drug efficacy and molecular markers to assess the emergence of AR in STH control programs.

**Methods:**

A series of drug efficacy trials will be performed in four STH endemic countries with varying drug pressure (Ethiopia and Brazil: low drug pressure, Lao PDR: moderate drug pressure and Tanzania: high drug pressure). These trials are designed to assess the efficacy of a single oral dose of 400 mg albendazole (ALB) against STH infections in school-aged children (SAC) by microscopic (duplicate Kato-Katz thick smear, Mini-FLOTAC and FECPAK^G2^) and molecular stool-based diagnostic methods (quantitative PCR (qPCR)). Data will be collected on the cost of the materials used, as well as the time required to prepare and examine stool samples for the different diagnostic methods. Following qPCR, DNA samples will also be submitted for pyrosequencing to assess the presence and prevalence of single nucleotide polymorphisms (SNPs) in the β-tubulin gene. These SNPs are known to be linked to AR in animal STHs.

**Discussion:**

The results obtained by these trials will provide robust evidence regarding the cost-efficiency and diagnostic performance of the different stool-based diagnostic methods for the assessment of drug efficacy in control programs. The assessment of associations between the frequency of SNPs in the β-tubulin gene and the history of drug pressure and drug efficacy will allow the validation of these SNPs as a marker for AR in human STHs.

**Trial registration:**

The trial was retrospectively registered the 7^th^ of March 2018 on Clinicaltrials.gov (ID: NCT03465488).

## Introduction

Soil-transmitted helminths (STHs) include *Ascaris lumbricoides*, *Trichuris trichiura*, and two hookworm species, namely *Necator americanus* and *Ancylostoma duodenale*. Global estimates indicate that more than 1.4 billion people are infected with at least one of the four STH species [1]. They are responsible for an estimated 3.3 million disability-adjusted life years (DALYs) of which 1.2 million occurred in children which is the highest burden among all neglected tropical diseases (NTDs) [2]. Preventive chemotherapy (PC) is the main strategy to control the morbidity caused by STHs. This entails the periodic administration of a single, oral dose of albendazole (ALB; 400 mg) or mebendazole (MEB; 500 mg) mainly to preschool-aged (preSAC) and school-aged children (SAC) through a school-based PC programs [3]. However, as part of the control program for lymphatic filariasis—another NTD which share geographical distribution with STHs—ALB is also co-administered with ivermectin to the whole community [4, 5]. Powered by the London Declaration on NTDs, the global coverage of children in PC programs has increased from ~30% in 2011 to 63.6% in 2016 [6], and, if the goal of covering at least 75% of children by 2020 will be reached, over 900,000 DALYs will be averted [7]. The laudable long-term aim is to eliminate STHs as a public health problem, and to eventually declare targeted geographical areas free of infections [8].

However, this high level of drug pressure makes PC programs highly vulnerable to the development of anthelmintic resistance (AR). First, we are relying on two drugs (ALB and MEB) of the same class (benzimidazole (BZ) drugs), and with the same mode of action (the inhibition of the polymerization of microtubules). Hence the emergence of AR is likely to occur as drug donations expand. This has been substantiated in veterinary medicine [9–11], where AR has developed within a decade of the introduction of every anthelmintic class [12]. Moreover, the development of AR against one BZ drug would most likely be accompanied by poor anthelmintic drug efficacy of the other BZ drug. Second, drugs are administered in single doses and, although a single dose is operationally justified, it never achieves 100% efficacy [13–16]. Consequently, this practice may further select for the development of AR when suboptimal doses are widely applied over a significant period. in light of breaking transmission of soil-transmitted helminthiasis there is growing interest to move from a school-based towards a community-based approach, which will further reduce the worm population that is not exposed to drugs [17, 18]. Finally, few anthelmintic drugs are licensed for the treatment of STH infections in humans [19, 20]. Thus, should AR against BZ drugs eventually emerge and spread, PC-based control of STHs will be even more limited than at present with few acceptable alternative options. This re-enforces the urgent necessity for increased accessibility of anthelmintic drugs of different anthelmintic classes and thoroughly designed surveillance systems that allow for the detection of any changes in anthelmintic drug efficacy arising through the evolution of AR in these helminths.

In 2013, WHO developed a manual to evaluate drug efficacy (WHO 2013). And although a number of countries used this manual to evaluate the efficacy of the anthelminthic used in their programme, a systematic surveillance system to monitor drug efficacy and emergence of AR is lacking. One of the main reasons for this lack of monitoring systems is the absence of a framework that guides and supports health-care decision makers in planning, performing and reporting surveys. The development of such a framework is not straightforward [21]. Moreover, PC programs typically operate in resource-constrained settings, and therefore it is indispensable that health-care decision makers have some pliancy to minimize financial and technical resources, while assuring a reliable assessment of the drug efficacy and spread of AR [22–25]. Important obstacles to globally monitor patterns of changing drug efficacy and emergence of AR are (i) the need for diagnostic laboratories with experienced technicians to perform the surveys, and experienced staff to analyze and report the data; (ii) the absence of a quality assurance system that guarantees data of high quality; (iii) a validated marker linked to AR; (iv) on-site diagnostic methods that allow for early detection of AR, and (v) the lack of overall guidance in designing surveys to monitor drug efficacy in PC programs.

To conclude, AR is a real threat for PC programs targeting human STHs. To establish a surveillance system and to further ensure the efficacy of the administered drugs, there is a need for (i) diagnostic methods that effectively mitigate important obstacles of performing, analysing and reporting drug efficacy surveys in resource poor settings, and a validated molecular marker to detect emergence of AR at an early stage, (ii) a surveillance system that monitors global patterns of drug efficacy and AR and (iii) tools to plan routine AR monitoring, and to follow-up global changes in drug efficacy and spread of AR over time. Each of the aforementioned needs will be addressed in a separate work package of the Starworms project (STop Anthelmintic Resistant Worms; www.starworms.org). **The main objective** of the project is to **strengthen the monitoring** and **surveillance** of **drug efficacy** and **AR** in programs aimed at eliminating and controlling **STH infections** in humans.

This document describes the rationale, specific objectives and methods/design, and discusses the expected output and challenges for work package 1 of the Starworms trial which aimes to evaluate stool-based diagnostic methods to assess drug efficacy and BZ resistance markers to assess the emergence of AR. For more details on the other work packages, we refer to the project website [26].

### Introduction to work package 1

Currently, the reduction in number of eggs excreted in stool after drug administration (egg reduction rate, ERR) is the recommended method for monitoring the efficacy of anthelmintic drugs against STHs [27]. In contrast to other available assays, it allows for the assessment of the efficacy of any drug against all STHs [28–31].

Today, a variety of egg counting methods have been recommended by WHO for the assessment of drug efficacy [27], of which Kato-Katz thick smear is the most commonly applied. Egg counting still requires a minimum amount of laboratory equipment and experienced laboratory technicians to ensure quality of the data obtained [22, 24, 32]. Furthermore, it is essential that samples are analysed quickly after collection to ensure the visualisation of hookworm eggs and that results are adequately analysed, applying the most appropriate summary statistics [15, 27] and are then reported to the responsible authorities. There is often limited availability of laboratory capacity and a poor reporting of the results obtained. This prompts the need for an improved diagnostic method that enables (i) egg counts to be performed without the use of a microscope, (ii) automated egg counting, and (iii) submission of results from remote locations *via* the internet for quality control of egg counts, analysis and reporting. Such a method would eliminate the need for a microscope or highly skilled technicians/clinicians or administrators while providing and centralizing drug efficacy results.

A method that largely meets this target product profile is the FECPAK^G2^ platform. Recently, it has been launched as a complete remote-location diagnostic method for sheep/cattle farmers and their veterinarians to assess the intensity of helminth infections and efficacy of drugs [33]. The platform accumulates helminth eggs into one microscopic view after which digital images are taken [34]. Images are stored by the associated software and can be uploaded to a remote server when an Internet connection is available. Later, a web-based laboratory technician can count the eggs visible in the images, after which the results are returned to the user by e-mail. The FECPAK^G2^ platform thus potentially eliminates the need for skilled technicians on-site. The online software allows easy access for quality control of egg counting and the production of standardized analysis and reports. More importantly, it opens the door to automated egg counting by egg recognition software [35]. Recently, Ayana et al. (in press) [36] modified and optimized a FECPAK^G2^ protocol for the detection and quantification of human STH eggs in stool. However, it remains unclear whether it provides equivalent ERR results to those obtained by diagnostic methods recommended by WHO, and whether it would result in more efficient use of financial and technical resources under field conditions.

From a research perspective, there is a growing interest to apply quantitative polymerase chain reaction (qPCR) for the assessment of drug efficacy. In contrast to the egg counting methods, qPCR can differentiate the different hookworm species, and thus allow evaluation of BZ efficacy against the different hookworm species [37, 38]. This is of particular interest given that there could be differential susceptibility towards BZ drugs among hookworm species, and that there is increasing evidence of zoonotic transmission of *Ancylostoma ceylanicum* between dogs and humans [39–42]. Although studies have linked amount of DNA with egg output [37, 43], to date, qPCR has not yet been applied for the assessment of drug efficacy.

Early detection of BZ resistance is essential to anticipate the efficacy of drugs in STH control programs, as it is more difficult to mitigate the spread of AR when the initial frequency is already high [44]. However, both *in vivo* (e.g. ERR) and *in vitro* assays (e.g. egg hatch assay) lack the sensitivity to detect the emergence of AR at an early stage. For example, in animals ERR was only able to detect AR when the proportion of resistant STHs exceeded 25% [45], a proportion that may impede mitigating the spread of AR. A more sensitive alternative is a molecular test based on resistance-associated mutations in targeted genes. Due to the unfortunate and costly experiences of AR in veterinary medicine, BZ resistance has been researched in detail in animal STHs, providing strong evidence of molecular markers associated with BZ resistance. An overview of the markers for BZ resistance in animal STH is provided by Von Samson-Himmelstjerna et al., [46].

Generally, BZ resistance in animal STHs is caused by single nucleotide polymorphisms (SNPs) in the gene encoding β-tubulin at codons 167 (TTC to TAC), 198 (GAA to GCA) or 200 (TTC to TAC), but the relative association of these SNPs with BZ resistance varies considerably across animal STH species [47–49]. Various methodologies to detect and quantify these SNPs in animal STH have been developed through an international Consortium for Anthelmintic Resistance SNPs (CARS), [50] of which some have now also been developed and applied for human STHs [29, 30, 51–53]. The few studies assessing SNPs in human STHs suggest that (i) polymorphisms are predominantly found in codon 200, and (ii) that resistance-associated mutations increased after drug administration (seen for *T*. *trichiura*), (iii) but that there was no clear association with reduced drug efficacy. However, the results should be interpreted with caution. First, they were based on a small number of participants (ranging from 3 to 31 participants) across a limited number of geographical areas (Kenya, Haiti, Panama and Tanzania). Second, STH data were collected applying a variety of study methodologies. For example, the samples originated from a wide range spectrum of the population (pre-SAC, SAC and adults) and were examined applying different egg counting methods (Kato-Katz thick smear, McMaster egg counting method and FLOTAC), which makes comparison across studies difficult.

Most technologies to assess SNPs linked to BZ resistance are only available in well-equipped laboratories. Recently, Rashwan et al., [54] published a loop-mediated isothermal amplification (LAMP) assay for the assessment of β-tubulin polymorphisms in human STHs. Due to its simplicity, ruggedness and low cost, LAMP could provide major advantages in detecting AR on-site. However, the method needs to be further validated on field samples. Another strategy to further reduce the operational costs is to apply a pooled examination strategy. Examination of pooled stool has already proved to allow for reduction in technical and financial resources for other egg counting methods such as Kato-Katz thick smear [55].

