#### qPCR

All DNA extracts will be analyzed for the presence of *A*. *lumbricoides*, *T*. *trichiura*, *N*. *americanus* and *A*. *duodenale* DNA using qPCR assays previously described [37, 63, 64]. S9 Info provides a detailed SOP on how we will perform the qPCR. The output of the qPCR analysis will be expressed in genome equivalents (GE) per ml DNA extract.

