#### Pyrosequencing

In two subsets of the DNA samples, we will apply a previously described pyrosequencing protocol [30, 52] to determine frequency of mutant SNPs in the three codons of the ß-tubulin associated with BZ resistance. The first subset will consist only of baseline DNA samples, and will be used to assess the association between drug pressure history and the corresponding frequency of mutant SNPs linked to BZ resistance. Per study site, 60 baseline DNA samples positive for each STH species (*Ascaris*, *Trichuris* and hookworm) will be randomly selected from the available baseline DNA samples. To avoid these samples representing one school or one level of individual response to ALB, selection of the samples will be proportionately to the total number of cases per school and individual drug response (Table 3).

**Table 3 pntd.0006912.t003:** Classification of the individual response to a single oral dose 400 mg ALB against STH based on the individual egg reduction rate (iERR).

STH	Cured	Responder	Poor responder	Non-responder
***Ascaris***	iERR = 100%	iERR ≥ 95%	85% ≤ iERR < 95%	iERR < 85%
***Trichuris***	iERR = 100%	iERR ≥ 50%	40% ≤ iERR < 50%	iERR < 40%
**Hookworms**	iERR = 100%	iERR ≥ 90%	80% ≤ iERR < 90%	iERR < 80%

We will use a second set of DNA samples to assess the association between individual responses to ALB by pyrosequencing the ß-tubulin gene. At each site, samples from at least 30 participants who were cured (baseline samples only) and from at least 30 participants who were still excreting eggs at follow-up (both baseline and follow-up samples) will be selected for each STH species separately. Participants which still excreted eggs will be stratified, into ‘responders’, ‘poor responders’ and ‘non-responders’. This stratification will be based on WHO thresholds used for classifying the efficacy into ‘satisfactory’ (‘responders’), ‘doubtful’ (‘poor responders’) and ‘reduced’ (‘non-responders’) [27] (Table 3). A total of 10 participants will be randomly selected for each stratum. Total DNA will be extracted from these stool samples and sent for pyrosequencing at McGill University (Canada).

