### Assess associations between frequency of SNPs linked to BZ resistance measured by pyrosequencing and history of drug pressure and drug efficacy

To assess the association between mutant SNPs linked to BZ resistance and history of drug pressure, a permutation test will be applied to evaluate differences in frequency of mutant SNPs linked to BZ in the baseline samples across the study sites. Tukey’s method will be applied for pair-wise comparisons between the study sites.

To assess the association between mutant SNPs linked to BZ resistance and drug efficacy, a permutation test will be applied to evaluate any difference in frequency of mutant SNPs linked to BZ across the four levels of individual response to ALB (Table 3). Tukey’s method will be applied for pair-wise comparisons between the four levels of individual response.

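### The hookworm comparison of SNP frequency across ALB response classes ignores hookworm species; if the species differ in both response and measured SNP frequency, it can show an association that exists within neither

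*Protocol article*

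**What the plan says.** The Introduction describes the soil-transmitted helminths as including *Ascaris*, *Trichuris* "and two hookworm species, namely" *N. americanus* and *A. duodenale*. The Introduction to work package 1 says that "there could be differential susceptibility towards BZ drugs among hookworm species", and that, unlike egg counting, "qPCR can differentiate the different hookworm species". The qPCR section carries this through: "All DNA extracts will be analyzed for the presence of" both hookworm species, as separate targets.

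The SNP analysis does not. In the Pyrosequencing section the baseline subset is "60 baseline DNA samples positive for each STH species" per site, with hookworm counted as one of three. Table 3 gives one set of individual egg reduction rate cut-offs for all hookworms. The second subset takes at least 30 cured participants and 10 from each of three egg-excreting classes per site, again for hookworm as a whole. The analysis section for this objective uses a permutation test to "evaluate any difference in frequency of mutant SNPs linked to BZ across the four levels of individual response to ALB", with Tukey comparisons, and a similar test across sites. Neither test mentions hookworm species.

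The Discussion says in advance how results will be read: if the SNPs matter, mutant frequency should rise with drug pressure and with poorer individual response. It warns that trends would show association and not cause, that some response classes may not fill, and that the tests are imperfect. It does not mention hookworm species mix.

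**The concern.** An individual egg reduction rate for hookworm comes from eggs that microscopy cannot assign to a species, and the SNP frequency is compared for hookworm as one group. Suppose one species responds less well to ALB. Its share of infections will then be larger among poor responders and non-responders than among the cured. If that species also shows a different SNP frequency, through natural polymorphism or through how the assay reads it, the class means will differ because the species mix differs. With the higher frequency in the less responsive species, they rise as response falls.

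That is the pattern the Discussion would take as support for the marker, and the Abstract speaks of validating these SNPs. A marker carried into the surveillance work package on this evidence could be tracking species and not resistance. The confounder can be foreseen from the article's own text and will be measured on the same extracts.

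**Working it through.** The article gives no power or sample-size figure for this comparison, so there is none to reproduce. The check asks when the planned test rejects although no SNP affects response within either species.

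**Inputs from the article.** Class sizes per site are 30 cured and 10 in each of three other classes. That is 30 + 3 × 10 = 60 per site and 4 × 60 = 240 over four sites. No significance level is stated for this analysis; 0.05 is borrowed from the sample size section.

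**Assumed inputs (not in the article).** Each stool holds one species. Probabilities of being cured, responder, poor responder and non-responder are 0.60/0.25/0.07/0.08 for species 1 and 0.40/0.28/0.12/0.20 for species 2. The odds ratio for non-responder versus cured is therefore (0.20/0.40)/(0.08/0.60) = 3.75. Species 2 makes up 10%, 30% or 50% of infections. SNP frequencies follow a beta distribution with precision 20 around the species mean.

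**Mechanism.** With overall share π, the share of species 2 in a class is q = π·p₂/(π·p₂ + (1−π)·p₁). For π = 0.30:
- cured: 0.120/(0.120 + 0.420) = 0.22
- responder: 0.084/(0.084 + 0.175) = 0.32
- poor responder: 0.036/(0.036 + 0.049) = 0.42
- non-responder: 0.060/(0.060 + 0.056) = 0.52

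With mean SNP frequencies of 3% and 15%, the expected class mean is 3% + 12% × q. That gives 5.7%, 6.9%, 8.1% and 9.2%: a rising trend with no effect inside either species. If the two SNP frequencies are equal, the second term vanishes and there is no trend.

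**Rejection rates** (1,000 simulated trials per cell, 299 permutations each, nominal 5%):

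| Setting | 10% share | 30% share | 50% share |
|---|---|---|---|
| Response differs, SNP equal (5%/5%) | 6.0% | 4.4% | 5.7% |
| SNP differs (3%/15%), response equal | 5.1% | 5.5% | 4.0% |
| Both differ, SNP 3%/8% | 14.9% | 29.7% | 29.3% |
| Both differ, SNP 3%/15% | 31.5% | 61.9% | 60.6% |
| Both differ, 3%/15%, permuted within species | 4.7% | 5.7% | 5.0% |

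The simulation error at 5% is √(0.05 × 0.95/1000) = 0.7 points, so the first two rows and the last are compatible with 5%.

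**Second set of assumptions.** An F test stood in for the permutation test, with the same totals (120/40/40/40), per-sample SD of 4 points and 2% SNP frequency in one species. Rejection was 5.1% with equal species mix. When the other species' share rose 20/30/40/50% from cured to non-responder, it was 17.7% (2% versus 5%) and 60.9% (2% versus 10%). When the share rose 10/30/50/70%, it was 55.6% and 99.6%. The implied odds ratios are (0.5/0.5)/(0.2/0.8) = 4 and (0.7/0.3)/(0.1/0.9) = 21, so the upper results rest on an extreme input.

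**The case against.** The strongest objection is that the second condition has no support in the documents. Nothing gives SNP frequencies in *N. americanus* or *A. duodenale*. The nearest statement, that "the relative association of these SNPs with BZ resistance varies considerably across animal STH species", concerns the link between SNP and resistance in animal parasites, not background frequency in human hookworms. The first condition is only raised as a possibility, and the species mix at the sites is not given. If one species dominates, the problem nearly disappears. This stands, and it makes the point conditional.

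A reader might infer that a species difference in drug response is enough by itself. It is not: with equal SNP frequencies the test stayed at about 5%. A reader might also infer that the permutation test loses its type I error level. It does not for the null it states. If species mix makes the frequencies truly differ between classes, rejection is correct. The fault is in interpretation: the difference may not mean that the SNP affects response.

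The article does not say which hookworm species the pyrosequencing assay reads. If it reads only one, the mechanism above cannot operate. The problem then becomes a mismatch, with one species' SNPs set against an egg reduction rate that may reflect both.

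The Discussion's caution about association and cause helps, but it does not name species mix. An unseen analysis plan could add stratification. What the article does fix is one hookworm sampling group, one classification and one test without species.

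**Conclusion.** The point holds conditionally. If hookworm species differ in both ALB response and measured SNP frequency, the unstratified hookworm comparison can show an association without any within-species SNP effect, and the Discussion would read it as support for the marker. Under the permutation simulation's assumptions, a nominal 5% test rejects in about 15% to 62% of trials when both conditions hold, and in about 5% when either is absent. These figures show the mechanism and do not predict the trial's result: the response probabilities, species shares and SNP frequencies are all assumed. The simulations also fill every response class, which the Discussion itself doubts will happen.

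The between-site hookworm comparison is open to a parallel problem if species mix differs by site and the species differ in measured SNP frequency. That was reasoned, not simulated.

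**What to change.** In the analysis section for this objective:

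- Use the planned qPCR to label each hookworm extract *N. americanus* only, *A. duodenale* only or mixed.
- Run the hookworm SNP-by-response permutation test with labels permuted within these three strata, keeping mixed extracts as their own stratum.
- Add a sensitivity analysis restricted to single-species extracts. The proportions of the two species can still vary within the mixed stratum, and the simulated recovery to 4.7% to 5.7% assumed one species per stool.
- Treat the between-site hookworm comparison by species as well.

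In the Pyrosequencing section, state which hookworm species the assay reads. If only one, set its SNP frequency against response in extracts where qPCR finds that species alone.

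Leave the selection numbers as they are. Choosing only single-species extracts, or dropping mixed ones from the marker conclusion, is not needed and would shrink response classes that may already be hard to fill.

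The change needs analysis wording only and no new laboratory work, since the qPCR is already planned on all DNA extracts. The cost is some loss of precision where species strata are small.
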